## Abstract

**Background:**

Measuring vital signs (VS) is important in potentially unwell children, as a change in VS may indicate a more serious infection than is clinically apparent or herald clinical deterioration. However, currently available methods are not suitable for regular measurement of VS in the home or community setting, and adherence can be poor. The COVID-19 pandemic highlighted a need for the contactless measurement of VS by nonclinical personnel, reinforced by the growing use of telemedicine. The Lifelight app is being developed as a medical device for the contactless measurement of VS using remote photoplethysmography via the camera on smart devices. The VISION-D (Measurement of Vital Signs by Lifelight Software in Comparison to the Standard of Care—Development) and -V (Validation) studies demonstrated the accuracy of the app compared with standard of care (SOC) measurement of blood pressure, pulse rate (PR), and respiratory rate (RR) in adults, supporting certification of Lifelight as a class I Conformité Européenne medical device.

**Objective:**

To support the development of the Lifelight app for pediatric patients, the VISION-Junior study is collecting high-quality data that will be used to develop algorithms for the measurement of VS (PR, RR, and oxygen saturation) in pediatric patients. The accuracy of the app will be assessed against SOC measurements made simultaneously with app measurements.

**Methods:**

The study is recruiting pediatric patients (younger than 18 years of age) attending the Sunderland Royal Hospital pediatric emergency department of the South Tyneside and Sunderland National Health Service Foundation Trust. High-resolution videos of the face (and torso in children younger than 5 years of age) and audio recordings (to explore the value of crying, wheezing, coughing, and other sounds in predicting illness) are made using the Lifelight Data Collect app. VS are measured simultaneously using SOC methods (finger clip sensor for PR and oxygen saturation; manual counting of RR). Feedback from patients, parents, carers, and nurses who use Lifelight is collected via questionnaires. Anticipated recruitment is 500 participants, with subtargets for age, sex, and skin tone distribution (Fitzpatrick 6-point scale). Early data will be used to refine the algorithms. A separate dataset will be retained to test the performance of the app against predefined targets.

**Results:**

The study started on June 12, 2023, and reached its recruitment target (n=532) in April 2024 after extending the deadline. Algorithm refinement is in progress, after which the performance of Lifelight will be compared with the SOC measurement of VS. The analyses are expected to be completed by mid-August 2024.

**Conclusions:**

Data collected in this study will be used to develop and assess the accuracy of the app for the measurement of VS in pediatric patients of all ages.

**Trial Registration:**

ClinicalTrials.gov NCT05850013; https://clinicaltrials.gov/study/NCT05850013

**International Registered Report Identifier (IRRID):**

DERR1-10.2196/58334

## Introduction

Measurement of vital signs (VS) is an essential part of clinical evaluation, providing important information about a patient’s health; importantly, a change in VS may herald a deterioration in clinical condition [1] and may precede the emergence of physical symptoms during the early stages of an infection [2]. High pulse rate (PR) and respiratory rate (RR) have been shown to predict hospital admission in children [3]. Infections such as influenza, scarlet fever, and chickenpox are common causes of morbidity and mortality in immunocompromised children [4,5]. Three-quarters of children who develop severe sepsis from infection have a comorbid condition such as asthma, diabetes, cystic fibrosis, or cancer. Sepsis carries a mortality rate of almost 50% in the most vulnerable children [6]. Treatment of infection in children can be expensive, especially if intensive care is required.

Given that monitoring of VS is important in clinically vulnerable children to aid early detection of infection [7], a robust method that parents can use at home to measure VS is likely to be beneficial and would support remote initial assessment [8]. The measurement of VS is time-consuming and requires trained staff and multiple pieces of equipment, some of which need regular calibration. Accurate measurement of blood pressure (BP) using a sphygmomanometer requires the use of the correct size cuff for the patient. The physical contact of equipment can be uncomfortable and distressing for patients, particularly those with learning disabilities. Stress can affect BP, PR, and RR, such that the measurements may not accurately reflect the patient’s state of health [7]. Standard of care (SOC) medical equipment is not suitable for regular measurement of VS in the home or community setting. Adherence to frequent VS monitoring using traditional technologies is low because of the inconvenience and stigmatizing nature of specialist hardware equipment (eg, thermometers, BP cuffs, and finger-clip oximeters) [7]. The COVID-19 pandemic has also highlighted the need for methods suitable for the remote or contactless measurement of VS that can be operated by people without specific medical training. The growing use of telemedicine since the pandemic also points to the need for easy but accurate measurement of VS.

Photoplethysmography (PPG) is an optical measurement technique that records changes in the light reflected from the skin surface due to volumetric changes in the facial blood vessels; small variations in perfusion provide valuable information about the cardiovascular system [9]. PPG has been used to measure PR [10,11], oxygen saturation [12], BP [13,14], and RR [10,15] and to detect atrial fibrillation [16].

Lifelight is an app being developed for the contactless measurement of VS using remote PPG via the camera on smart devices such as phones and tablets. The app captures the average color of regions of interest on the face 30 times every second for 60 seconds and sends these as red, green, and blue color values to a central server for processing, yielding VS values. The VISION-D (Measurement of Vital Signs by Lifelight Software in Comparison to the Standard of Care—Development) study in 2018-2019 measured VS in 8585 patients and healthy volunteers simultaneously using the app and SOC methods. The data were used for machine learning to develop the algorithms used to calculate VS. The subsequent VISION-V (Validation) study demonstrated the accuracy of the app compared with SOC methods for measuring PR, RR, and diastolic BP [17], providing the basis for the current Class I Conformité Européenne (CE) mark [18]. The app also received ISO 13485:2016 certification in August 2023 [19], and the accuracy of the app for measuring PR and BP against ISO standards in adults with stage 1 hypertension has recently been reported [20]. The VISION-MD (multisite development) study evaluates the app versus SOC in patients with a wide range of clinically relevant VS values, including critically ill patients, and across the full range of skin tones [21]. In VISION-MD, high-resolution full-face videos of participants’ faces have been recorded, which has proved instrumental in improving the accuracy of VS measurement compared with the VISION-D and -V studies.

The VISION-Junior study explores the measurement of VS using a Lifelight app developed for pediatric patients (aged 18 years or younger) attending the pediatric emergency department. As in VISION-MD in adults, high-resolution full-face videos will be recorded. In younger children (younger than 5 years of age), the video will also include the torso to increase the surface area from which the signal is recorded, and because the torso is likely to move less than the face. Audio data will also be recorded, as crying, wheezing, coughing, and other sounds can also predict illness in children [22,23].

The aim of the VISION-Junior study is to assess whether the app can be used to accurately measure VS in pediatric patients. This protocol describes the collection of data that will initially be used to develop the algorithms for the measurement of VS in children. Later data will be used to assess the accuracy of the app across the range of VS values encountered in children of different ages. The objectives are as follows.

The primary objective is to collect data to support the development of the app for the accurate measurement of PR, RR, and oxygen saturation in pediatric patients and to assess the accuracy of measurements against SOC methods. Secondary objectives are: (1) to assess—using the collected PPG data—whether other (direct or indirect) measurements can be made using the app, including temperature, BP, PR variability, and audio analysis; (2) to evaluate the impact of subject-specific variables on the PPG VS measurements (eg, medication, cosmetics, facial or body hair, and skin tone); (3) to obtain data to understand patient and parent or guardian or carer habits and preferences for VS measurement using questionnaires (Multimedia Appendices 1 and 2); and (4) to assess the usability of Lifelight Junior for measuring VS in pediatric patients through questionnaires completed by participating health care professionals (Multimedia Appendix 3).

Most of the data collected in the study will be used to train the app algorithms to measure VS in pediatric patients. The remaining data will be kept separate and used to assess the accuracy of the algorithms at regular intervals during the data collection period. The study delivery process will be responsive to this learning curve to increase the likelihood that the predetermined accuracy target for each VS estimation is achieved by the study end.

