### Sample Size

An estimated 500 pediatric patients (18 years old or younger) will be recruited into the study. This sample size is informed by the previous VISION-D, VISION-MD, and VISION-Acute studies [17,21]. However, the sample size cannot be formally calculated because it depends on the incremental improvement in the performance of the app achieved through machine learning using the training data generated early in the study. The split between training and testing data will be determined during the study according to the quality of the data collected. The study management team monitors the progress of data collection and accuracy and updates the study teams weekly. The study will continue until the accuracy of the app for measuring VS in pediatric patients is sufficient for various clinical use cases.

In addition, recruitment targets according to age, sex, Fitzpatrick skin tone, and medical history have been defined, as shown in Table 3, to ensure accuracy in a broad range of clinically relevant patients.

**Table 3 table3:** Demographic and medical history recruitment targets.

	Targets
Age	≥12% aged 0-1, 1-2, 2-5, 5-11, 11-14, 14-18 years
Sex	≥40% male; ≥40% female
Skin tone	15% of participants will have Fitzpatrick skin tones 4, 5, or 6 (this is not a hard target as achieving this figure depends on the demographic diversity of the study region)
Medical history	≥40% in each of the following categories: Febrile (≥38 °C) Afebrile Ill (as judged by the clinical staff); to ensure a spread of conditions, no more than 50% of recruited patients will have an acute respiratory illness (eg, bronchiolitis, asthma, virus-induced wheeze, pneumonia, and croup) Well, including pediatric patients with a minor injury

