### Data Analysis

All statistical analyses will be performed using Python (Python Software Foundation). Training data will be used for machine learning to improve the performance of Lifelight Junior for measuring VS in pediatric patients. Appropriate machine learning models will be developed according to the data collected. This is likely to include signal processing and measurement algorithms for PR and RR, and multilayer neural network-based approaches for BP, similar to those used in the adult version of the app.

The separate set of test data will subsequently be used to determine the performance of the app for measuring VS in pediatric patients. Correspondence between VS measurements predicted by the app and the measurements taken manually using SOC methods will be compared using regression coefficients, mean error, and SD, and compared against the performance targets set out in Table 2. An accuracy target will be considered met if the mean error and SD for the app measurements are at least equal to the target (Table 2). Heat maps or scatter plots will also be developed.

Linear regression will be used to assess the impact of skin tone on the accuracy of the app for measuring each VS, using the Fitzpatrick skin tones as the explanatory variable.

Quantitative data from the questionnaires will be summarized. Thematic analysis will be used to analyze free-text responses to identify perceptions of the app and variations in the way patients, their parents or carers, and health care professionals interact with it and any challenges they encounter.

All analyses will be completed per protocol since there is no intention to treat. There will be no imputation of missing or implausible data, and any missing, implausible, or problematic readings will be excluded from analysis.

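### The only data held apart from training are scored repeatedly to steer the study, and nothing excludes them from the final accuracy comparison

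*Protocol article*

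**What the plan says.** Four statements in the protocol article bear on this.

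- **Partition (Introduction, last paragraph).** "Most of the data collected in the study will be used to train the app algorithms to measure VS in pediatric patients". The rest is the only other part named: "The remaining data will be kept separate and used to assess the accuracy of the algorithms at regular intervals during the data collection period".
- **Use of the interim scores (same paragraph).** "The study delivery process will be responsive to this learning curve to increase the likelihood that the predetermined accuracy target" for each vital sign is met by the end of the study.
- **Split and stopping (Sample Size).** "The split between training and testing data will be determined during the study according to the quality of the data collected". On monitoring: "The study management team monitors the progress of data collection and accuracy and updates the study teams weekly". On when to stop: "The study will continue until the accuracy of the app for measuring VS in pediatric patients is sufficient for various clinical use cases". The same section gives a recruitment figure of about 500 and says that it could not be formally calculated.
- **Final analysis (Data Analysis).** "The separate set of test data will subsequently be used to determine the performance of the app", with the result judged against the targets in Table 2. For pulse rate the target is an RMSE of at most 5 beats per minute.

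The Results section reports that recruitment was extended so that 500 could be reached, that 532 had been recruited by April 5, 2024, and that algorithm refinement was continuing at that point.

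**The concern.** Assessing accuracy against standard of care is part of the primary objective. A held-out set gives an unbiased accuracy estimate only if its results have not influenced what is later reported from it. Here the held-out data are scored repeatedly, and the scores are meant to change the conduct of the study in the direction of passing. The boundary between training and test data also stays open while this goes on. If the same data then supply the final figure, a favourable chance fluctuation at any check can carry through to the result.

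The error runs one way. Reported accuracy would tend to look better than it is, and an algorithm that narrowly misses a target would be declared to meet it more often than a single clean test would allow. The article presents the app as a way for nonexperts to detect early deterioration in vulnerable children, so an overstated accuracy claim matters.

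Separately, a rule to continue until accuracy is good enough cannot stand beside a recruitment target of about 500 without saying which one governs.

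**Working it through.** **1. Is an untouched set defined?** The Introduction names two parts, training data and the remainder, and the remainder is scored during collection. The Data Analysis section draws the final figure from the separate set. The Abstract says a separate dataset is retained for testing, and the Introduction says later data will be used to assess accuracy. None of these places defines a third part, a lock, a single-use rule or an exclusion of interim-scored data. Read literally, the interim-scored set and the final test set are the same.

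**2. Is there a plan figure to reproduce?** No. The 500 is expressly not derived by formula, and no test-set size, number of checks or error SD is given. What follows illustrates the effect under stated assumptions and does not estimate the bias in this study.

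**3. Assumptions.** Pulse rate errors are normal with mean zero. The target is RMSE ≤ 5 (Table 2). The test set has n = 100. The true RMSE σ is above 5, so the target is truly missed.

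**4. One look at a locked set.** The pass probability is P(χ²₁₀₀ ≤ 100 × (5/σ)²).

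- σ = 5.25: 100 × (5/5.25)² = 90.70, probability 0.264
- σ = 5.5: 100 × (5/5.5)² = 82.64, probability 0.104
- σ = 6: 100 × (5/6)² = 69.44, probability 0.009

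**5. One fixed set reused for ten algorithm versions.** All versions have the same true RMSE, and their errors on the same participant correlate 0.5 to 0.9. A pass is declared if any version has an observed RMSE ≤ 5. Recruitment ran 298 days (about 43 weeks) from June 12, 2023 to April 5, 2024, so ten checks would be roughly monthly. Simulation gives:

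| True RMSE | One look | Ten versions, correlation 0.9 | Ten versions, correlation 0.5 |
|---|---|---|---|
| 5.25 | 26% | 52% | 84% |
| 5.5 | 10% | 27% | 54% |
| 6 | 0.9% | about 4% | about 7.5% |

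**6. Effect on the reported figure.** At σ = 5.5, one look reports a mean RMSE of 5.48 to 5.49. With ten versions, reporting the first pass or otherwise the last version, the mean is 5.44 at correlation 0.9 and 5.21 at 0.5. Relative to one look, the optimism is about 0.04 to 0.28 beats per minute.

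**7. Sensitivity to test-set size.** At σ = 5.5 with n = 50, one look passes 20% of the time and ten versions 44% to 75%. With n = 150 the figures are 6% and 17% to 38%. The level moves a good deal; the direction does not.

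**8. The stopping rule beside the conduct.** The Sample Size section makes the end of the study depend on accuracy. The Results section says the extension was made to reach the count of 500, and that refinement was still under way once 532 had been recruited. The two statements describe different stopping rules.

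**The case against.** Several points on the other side are fair.

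**Tuning.** A reader might infer that the algorithms are fitted to, or selected on, the separate data. The text does not say so. It says that study delivery responds, which could mean recruitment mix or recording practice. That stands, and the ten-version calculation therefore shows what reuse could do, not what is documented. Steering by the scores while reporting from the same data is still enough to remove independence.

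**Stopping on accuracy.** A reader might infer that the study ended at the first favourable check. Under such a rule, with one unchanging algorithm and looks at 10, 20, up to 100 participants, the false-pass rate at a true RMSE of 5.5 would be about 58%; with looks from 50 to 100 it would be about 28%. The documents do not support applying those figures here. Recruitment appears to have ended on the count, and the article does not say which data were to show that accuracy was good enough.

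**A later, untouched evaluation.** The Abstract's retained dataset, the Introduction's reference to later data and the timing in the Data Analysis section leave room for one. They do not define it, and none says that interim-scored participants are left out.

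**Condensation.** An article can leave the mechanics of partitioning and locking to the full protocol. That would answer a complaint about silence. Here the article positively states repeated scoring of the held-out data and feedback from the scores.

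**Size.** The large absolute effects are confined to near misses, as the row for a true RMSE of 6 shows. Only pulse rate was modelled, not the respiratory rate or oxygen saturation targets.

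**Conclusion.** The point holds as a defect in the plan as written. The only data kept apart from training are scored at intervals and used to steer the study, the split is open until the study is running, and no section excludes those data from the final comparison. The Table 2 comparison is therefore not independent and would tend to be optimistic. This should be corrected before any target is declared met, because it touches the primary accuracy claim.

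The size is not determinable from the article. Under the assumptions above, reuse over ten versions multiplies the chance of a false pass roughly 2.6 to 5 times at a true RMSE of 5.5 (27/10.4 to 54/10.4). At a true RMSE of 6 the absolute risk stays below 8%.

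The documents do not establish that the algorithms were tuned on the test data, or that the study stopped because accuracy looked good. The accuracy-based stopping sentence is a conflict with the target of about 500, and it appears not to have operated.

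**What to change.** 1. Designate every participant scored at an interim check as validation data, or do all interim monitoring by participant-level cross-validation within the training data.
2. Take the final performance only from participants never used in training or interim scoring. Freeze the algorithm first, then score that set once.
3. Check that set against the Table 3 age and skin-tone mix, since a set drawn only from late recruits may not match it. Between December 20, 2023 and April 5, 2024, 532 − 303 = 229 participants were added, but nothing in the article shows that any of them remain unused.
4. If no such participants remain, report the accuracy as a development-stage estimate and do not declare the Table 2 targets met.
5. Replace the sentence on continuing until accuracy is sufficient with the recruitment target actually used.

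If a locked set already exists, stating how it was formed and that it was never scored at interim would settle the matter.

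Cost: wording in the protocol and analysis plan, somewhat fewer participants for training, and a final figure that may be less precise or less favourable. No further recruitment is needed if unused participants exist or if the fallback in item 4 is accepted.

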## Methods

The design and protocol for this study have been informed by the VISION-MD study [21] and earlier VISION studies [17].

### Participants and Recruitment

Approximately 500 pediatric patients are being recruited at the Sunderland Royal Hospital pediatric emergency department of the South Tyneside and Sunderland National Health Service (NHS) Foundation Trust. All pediatric patients (younger than 18 years of age) attending the pediatric emergency department are potentially eligible for the study. The exclusion criteria are critical illness (as judged by the treating physician), including unconscious patients, patients who were noncompliant in terms of excessive movement during the VS measurements, and patients whose parents, guardians, or carers do not speak English (required to give informed consent). The study aims to recruit according to age, sex, Fitzpatrick skin tone, and medical history criteria, as subsequently described.

The research nurse approaches the parents, guardians, or carers of potential participants identified by the clinical team about taking part in the study. Potential participants aged 17 or 18 years or the parents, guardians, or carers of younger children are provided with an ethics-approved information sheet explaining the study aims, what is involved, and the requirements for participation. Younger children also watch ethics-approved age-appropriate videos (for ages 5-10 and 11-16 years) explaining the study on a tablet device (Multimedia Appendices 4 and 5).

The information sheet and videos were developed in collaboration with the Young People Advisory Group North England and the South Tyneside and Sunderland NHS Foundation Trust Young Persons Group. These groups also provided feedback on the design of the study, consent/assent forms, and other study documents at 2 in-person meetings.

